### Data analysis

The Foresight map will be used as a basis to model relationships within and between the domains so as to demonstrate which elements of the system are changing, the strength of these changes, the elements that are resisting change and the implications of these relationships for childhood obesity.

The outlined datasets contain >75 % of the 65 variables within five domains of the Foresight map (individual physical activity, physical activity environment, individual psychology, social psychology and food consumption) and various techniques will be used to test the hypotheses. For hypothesis 1: HTV changes elements of local community-level systems that influence childhood obesity, a series of mixed effects linear regression analyses will be used. Prior to the analyses, a confirmatory factor analysis will be utilised to reduce the data within each of the Foresight domains so a factor score is obtained. Each of the factors will then be used as the dependent variable with the independent variable being study condition (HTV or non-HTV) interacting with time adjusted for hypothesised covariates. The resulting predictions will be plotted and compared to the changes in childhood obesity from Aim 1. Positive changes in each of the domains in HTC compared to non-HTC combined with positive changes in childhood obesity over the same time period would provide support for Hypothesis 1.

For hypothesis 2: Differential changes in local community-level systems have differential effects on the LGA policy environment, school environments, child behavior and subsequent weight status, a series of multi-level (individual and LGA) structural equation models will be used. The main area of interest will be the LGA level as it is the heterogeneity at this level that is important in testing hypothesis two. The first model will test the influence of each of the domains on one another plus policies within LGAs. The second will substitute school environments as the dependent variable, the third child behavior and the fourth child weight status. Child weight status will be calculated using the self-reported data from the PHS. These data will be used as they have corresponding adult data that can be used in calculating the systems-level exposures. Sensitivity analyses will be undertaken in order to calculate the differences in child weight status between the measured and self-report groups. Depending on findings, weightings may be used to correct the difference.

Using this approach, the impact of changes within each of the five domains can be quantified and the relative contribution of each domain to LGA policy environment (continuous score of number of obesity related policies calculated from the policy audits), school environments (continuous score calculated from the School Environmental Audits), child behaviour (proportion of children meeting the PA and sedentary guidelines and proportion meeting the fruit and vegetable consumption guidelines) and subsequent weight status (proportion of children with overweight and obesity) assessed over time. Model fit analyses (e.g., Aikake’s and Bayesian Information Criteria) will be used to determine the significance of the impact of the each of the domains of the system, individually and in total, both cross-sectionally and over time.

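### Aim 2 promises to show which system elements change and which resist change, but its described models work only on domain scores and cannot deliver that result

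*Protocol article*

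**What the plan says.** All of this is in the Protocol article, in the Data analysis section of Research plan aim 2.

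- **Purpose.** The Foresight map will be used to model relationships within and between domains, "so as to demonstrate which elements of the system are changing, the strength of these changes, the elements that are resisting change".
- **Hypothesis 1.** "HTV changes elements of local community-level systems that influence childhood obesity".
- **Data reduction.** Before the models are fitted, "a confirmatory factor analysis will be utilised to reduce the data within each of the Foresight domains so a factor score is obtained".
- **Model.** "Each of the factors will then be used as the dependent variable with the independent variable being study condition", interacting with time, in mixed effects linear regressions.
- **Criterion for support.** "Positive changes in each of the domains in HTC compared to non-HTC combined with positive changes in childhood obesity" over the same period.
- **Data.** "The outlined datasets contain >75 % of the 65 variables within five domains of the Foresight map".
- **Hypothesis 2.** The structural equation models also work by domain: "The first model will test the influence of each of the domains on one another plus policies within LGAs". The section closes by saying that "the impact of changes within each of the five domains can be quantified and the relative contribution of each domain" to the outcomes can be assessed.

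**The concern.** The stated purpose is a finding about elements: which moved, by how much, and which did not. The analysis that follows turns each domain into a common-factor score and then tests and interprets that score. Such a score mainly carries what its indicators share. It does not say which indicator produced a change, and two equally loaded indicators that move equally in opposite directions cancel to zero. The factor loadings describe how variables relate to the factor, not which variable changed by arm.

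This matters because many of the actions listed under Setting have specific targets, such as active transport planning, access to healthy food and food in sport and recreation centres. Uneven change inside a domain is therefore plausible. Followed as written, the plan could find little change in a domain score although some of its variables had shifted, and it could not name a changing or a resisting element in either case.

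**Working it through.** **1. The plan's own figure.** Counting the rows of Table 3 by domain:

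| Domain | Variables | No source or item | Covered |
|---|---|---|---|
| Physical activity environment | 13 | 1 | 12 |
| Individual physical activity | 11 | 2 | 9 |
| Social psychology | 16 | 4 | 12 |
| Individual psychology | 9 | 1 | 8 |
| Food consumption | 15 | 4 | 11 |
| Total | 64 | 12 | 52 |

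The text gives 65 variables and the table shows 64, a trivial difference. Coverage is 52/65 = 80%, which agrees with the stated figure of more than 75% when non-survey sources count. Counting only variables with a survey source gives 39/65 = 60%. So about 39 to 52 measured variables are reduced to five outcomes, with 8 to 12 covered variables per domain.

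**2. Level of each statement.** The purpose and hypothesis 1 speak of elements. The data reduction, dependent variable, criterion for support, hypothesis 2 models and closing quantification all speak of factors or domains. None of these models has a single variable as its outcome.

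**3. Attenuation when one indicator moves.** Assume k standardised indicators with equal weights and mean correlation r. The SD of their sum is √(k + k(k−1)r). If one indicator shifts by d SD, the score shifts by d/√(k + k(k−1)r) of its own SD.

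| k | r | Share kept | 0.5 SD becomes |
|---|---|---|---|
| 8 | 0.1 | 1/√13.6 = 0.271 | 0.14 |
| 8 | 0.3 | 1/√24.8 = 0.201 | 0.10 |
| 10 | 0.3 | 1/√37 = 0.164 | 0.08 |
| 12 | 0.5 | 1/√78 = 0.113 | 0.06 |

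The document gives no loadings or correlations, so r is an assumption. A regression factor score with equal loadings L gives the same result with r = L². For example, k = 8 and L = 0.6 gives 1/√(8 + 56 × 0.36) = 0.188.

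**4. Attenuation under other assumptions.**

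- *Several indicators move together* (m of them, share m/√(k + k(k−1)r)). For k = 8 and r = 0.3, four movers give 4/√24.8 = 0.80 and all eight give 1.61, so a shared change is not lost.
- *Unequal loadings.* With k = 8 and the other seven indicators at 0.6, the share kept is 0.07 if the moving item loads 0.3 and 0.55 if it loads 0.9.
- *Repeated item.* In Table 3, perceived environmental amenity serves five physical activity environment variables. If five of ten indicators are one and the same measure and all other correlations are 0.3, the variance of the sum is 25 + 5 + 20 × 0.3 + 50 × 0.3 = 51. The share kept is 5/√51 = 0.70.

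**5. Power for single items.** This is an illustration with 12 against 12 areas, as in the sample size section, using a two-sample t-test with shifts in area-level SD units.

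| Shift in one item | Modelled alone, α = 0.05 | Modelled alone, strictest step for 40 tests (0.05/40 = 0.00125) |
|---|---|---|
| 0.5 SD | 22% | 2% |
| 1.2 SD | 80% | 27% |

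Through the domain scores of step 3, the 1.2 SD shift has about 6% to 12% power at α = 0.05.

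**The case against.** The strongest reply is that the article never defines elements. If the word means domains, five domain scores do show what changes and what resists. That reading is strained. The introduction to Aim 2 separates 108 variables from seven domains, Table 3 works variable by variable, and the purpose statement speaks of relationships within domains as well as between them.

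A second reply is that the article says various techniques will be used and condenses a fuller document. But it then names the technique for each hypothesis, and both work by domain. The issue is a mismatch between two things the article does state, not an omitted detail.

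Other parts of the reply stand. A reader might infer that no element can be identified anywhere in the study. The document does not support that: Aim 1 follows physical activity, sedentary behavior, diet and school environments separately, and these overlap part of the map. A reader might also take a four- to nine-fold dilution as the expected loss. That figure requires a lone mover and equal weights, whereas HTV is a whole-of-system intervention, shared movement is not diluted, and Table 3 reuses items across variables. Finally, reducing correlated indicators before testing with few clusters is defensible, and item-level tests will have low power.

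**Conclusion.** The mismatch is real. The Aim 2 models as described cannot show which elements change or resist, although the plan says they will. The loss of information on a single variable can be large: about 0.11 to 0.27 of the shift remains if exactly one of 8 to 12 equally weighted indicators moves and the mean correlation is 0.1 to 0.5. This is an illustrative extreme under assumed correlations. Less is lost for high-loading or repeated items, and nothing when indicators move together. The point concerns Aim 2 only and leaves the randomised comparison of BMI z-score in Aim 1 untouched.

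**What to change.** - Keep the domain factor scores as the summary test of hypothesis 1.
- Add, as a secondary analysis, the same condition-by-time mixed model for each distinct measured Table 3 item that varies between areas. Merge variables that share an item, such as those resting on perceived environmental amenity, or energy density, fibre and nutritional quality. Leave out national-level sources, such as those for food abundance and food variety, because they cannot differ by condition.
- Report every estimate with its interval, with false-discovery-rate control (for example Benjamini-Hochberg) across the items.
- State in advance that a non-significant item is not evidence of resisting change.

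The cost is at most about 40 further models on data already planned, fewer after merging. The price is wide intervals and low power for single items with about 24 areas. If the sponsor does not want this, the objective and hypothesis 1 should be restated at domain level, which costs only a change of wording.

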	Social depreciation of labor	Degree to which manual labor is negatively valued in a given socio-cultural group	Not available from surveys	Employment demographics
			Can be inferred from the local demographics available on the Local Government websites	
	Sociocultural valuation of physical activity	Degree to which physical activity is positively valued in a given socio-cultural group	PHS	Social environment (social norms) for HEPA
	Walkability of living environment		PHS	Perceived environmental amenity
			Available from the Community Indicators Victoria website by LGA	
				School walkability
Individual physical activity	Degree of innate activity in childhood	Degree to which physical activity is part of typical childhood behavior	PHS and WHOCC surveys	Level of physical activity
	Degree of physical education	Degree to which people have learned to use their body (for labor, leisure and transport)	VPHS	Frequency and amount of vigorous physical activity in past week
			PHS	
				Physical Activity and sedentary
	Functional fitness	Level of physical fitness to perform daily tasks	VPHS	Self-reported health status
			WHOCC	
				Paediatric Quality of Life Inventory (PedsQL) [40]
	Learned activity patterns in early childhood	Degree of activity experienced by the foetus, newborn and child in early life through parental physical activity	Not available from surveys	
	Level of domestic activity	Level of physical activity exhibited in the domestic arena	VPHS	Physical activity at work
	Level of occupational activity	Level of physical activity associated to professional duties	VPHS	Physical activity at work
	Level of recreational activity	Degree to which people engage in physical activity for recreation	VPHS	Frequency and amount of vigorous physical activity in past week
			PHS	
				Physical Activity and sedentary
	Level of transport activity	Level of physical activity associated to transport	Not available from surveys	
			Available from the Community Indicators Victoria website by LGA for Melbourne metropolitan area only	
	Non-volitional activity (NEAT)	extent to which people engage in non-volitional activity (twitching etc.)	Not available from surveys	
	Parental modelling of activity	Degree to which parents act as a role model in physical activity related behavioral patterns	PHS	Parent physical activity
				Child physical activity
	Physical activity	Level of physical activity people engage in	VPHS	Frequency and amount of vigorous physical activity in past week
			PHS	

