				Physical Activity and sedentary
Social psychology	Acculturation	Degree to which a (dominant) culture is assimilated	VPHS	Country of birth
				Main language spoken at home
				Country of birth of mother
				Country of birth of father
	Availability of passive entertainment options	Availability of recreational options that involve only limited physical exercise (tv, computer games)	PHS	Sedentary behavior items
	Children’s control of diet	Degree to which children exert influence on dietary choices in a family	Not available from surveys	
	Conceptualisation of obesity as a disease	Degree to which people consider obesity to be an abnormal deviation from the healthy norm	Not available from surveys	
	Education	N/A	VPHS & PHS	Demographics
	Exposure to food advertising	N/A	Not available from surveys	Level of exposure to food advertising
			Available from the literature	
	Importance of ideal body-size image	Degree to which there is a dominant image of an ideal body size in a society	Not available from surveys	
	Media availability	Availability of media across formats	Not available from surveys	Data on availability of all types of media
			The Victorian Government digital innovation review Part B: The digital readiness of Victorian citizens	
	Media consumption	Degree to which people make use of the media offerings	Not available from surveys	Data on use of all types of media
			The Victorian Government digital innovation review Part B: The digital readiness of Victorian citizens	
	Parental control	Level of control exerted by parents on children’s choices	Not available from surveys	
	Peer pressure	Degree to which average citizens influence one another’s choices	PHS	Social environment (social norms) for Healthy Eating and Physical Activity
	Perceived lack of time	By all citizens, particularly those engaged in economic activity	PHS	Instrumental beliefs (facilitators & barriers, decisional balance) for Healthy Eating and Physical Activity
	Smoking cessation	Number of people quitting smoking	VPHS	Number of people smoking from one survey to the next
	Social acceptability of fatness	N/A	VPHS & PHS	Height and weight; BMI heterogeneity between LGAs
	Sociocultural valuation of food	Degree to which food is positively valued within a given socio-cultural group	PHS	Instrumental
	TV watching	Time spent watching tv	PHS	Sedentary behavior

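### The third Aim 2 model explains child behaviour with a predictor domain that itself contains child physical activity

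*Protocol article*

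**What the plan says.** The Aim 2 data analysis section tests hypothesis 2 with four multilevel structural equation models. The first concerns the domains and LGA policies. For the others: "The second will substitute school environments as the dependent variable, the third child behavior and the fourth child weight status". The child behaviour outcome is defined as "child behaviour (proportion of children meeting the PA and sedentary guidelines and proportion meeting the fruit and vegetable consumption guidelines".

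The predictors are the Foresight domains, and the stated aim is that "the impact of changes within each of the five domains can be quantified and the relative contribution of each domain" will be assessed. Under hypothesis 1 the same section says how a domain becomes a variable: "a confirmatory factor analysis will be utilised to reduce the data within each of the Foresight domains so a factor score is obtained".

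Table 3 (Aim 2, study design and sampling) lists what goes into each domain. Two rows of individual physical activity are child data:

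- *Degree of innate activity in childhood* is described as "Degree to which physical activity is part of typical childhood behavior". It is measured by level of physical activity, with source "PHS and WHOCC surveys".
- *Parental modelling of activity* lists a parent activity item and "Child physical activity", both from the PHS.

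Behaviours of the same kind appear in three further domains, without saying whose answers are used. Social psychology has "Sedentary behavior items" from the PHS and a television row. Individual psychology has fruit, vegetable, activity and sedentary items under *Desire to resolve tension*. Food consumption has daily fruit and vegetable intake in several rows. Table 2 shows that the PHS samples both adults and children, while the VPHS samples adults only.

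**The concern.** Hypothesis 2 asks whether differences in local systems lead to differences in child behaviour. If a predictor score includes child physical activity, and the outcome is partly the proportion of children active enough to meet a guideline, the two are associated by construction. The model can then credit the individual physical activity domain with an influence that is only the outcome correlated with itself.

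What is at stake is the interpretation of one of the four hypothesis 2 models, and within it the comparison of domains. A domain containing part of the outcome has an unfair advantage over the physical activity environment domain, which lists no such behaviour items. Choosing by AIC or BIC, as planned, gives no protection, because an overlapping predictor tends to improve fit.

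**Working it through.** The article gives no figure for this model, so there is nothing to reproduce. The check has two parts.

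**1. Tracing items against the outcome**

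| Domain | Outcome behaviour among its items | Respondent |
|---|---|---|
| Individual physical activity | Child physical activity, in two rows | Child, explicit |
| Social psychology | Sedentary items, television | PHS, not stated |
| Individual psychology | Fruit, vegetables, activity, sedentary (one variable) | PHS, not stated |
| Food consumption | Fruit and vegetables | VPHS (adults) and PHS, not stated |
| Physical activity environment | None | Not applicable |

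The source of the child behaviour outcome is not named. The PHS child sample and the Aim 1 school survey both measure guideline adherence. WHOCC is evidently the school survey, since Table 3 attributes the PedsQL to it. As the innate activity row draws on both sources, overlap arises whichever supplies the outcome.

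**2. How large the built-in association could be**

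Inputs from the document: 26 LGAs (school and participant recruitment) or 24 areas (sample size section), and k = 8 variables of the individual physical activity domain with a VPHS, PHS or WHOCC source (a count from Table 3). Assumptions not in the document: correlation ρ among the other items of 0.1 to 0.5; reliability *rel* of the child item against the outcome of 0.6 to 1.0; and no true relation between the other items and child behaviour.

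For an equal-weight score with m child items, the expected correlation with the outcome is

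r = m√rel / √[m + m(m−1)rel + (k−m)(1 + (k−m−1)ρ)]

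- m = 1, rel = 1, ρ = 0.1: 1/√(1 + 7×1.6) = 1/√12.2 = 0.29
- m = 1, rel = 0.6, ρ = 0.5: 0.775/√(1 + 7×4) = 0.775/√29 = 0.14
- m = 2, rel = 1, ρ = 0.1: 2/√(4 + 6×1.5) = 2/√13 = 0.55
- m = 2, rel = 0.6, ρ = 0.5: 1.549/√(3.2 + 6×3.5) = 1.549/√24.2 = 0.31

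Simulated rejection rates at two-sided 5%, over these ranges of ρ and rel:

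| Score | No child item | One of eight | Two of eight |
|---|---|---|---|
| Equal-weight mean | 5–6% | 9–30% | 31–90% |
| First principal component | 4–6% | 10–49% | 24–99% |
| One-factor maximum likelihood (n = 26) | – | 6–29% | 10–98% |

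The lowest rates occur when the other items are strongly intercorrelated and the child item is an imperfect proxy. The highest occur when the other items are weakly correlated and the child item copies the outcome.

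With the equal-weight score the spurious correlation is positive. With principal-component weights it can take either sign: one child item with ρ = 0.1 and rel = 1 (n = 24) gave a mean correlation of 0.04 but 49% rejections. The upward direction therefore depends on the child item loading positively on the domain, as an activity domain would intend.

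**The case against.** The article contains sentences that favour adult-based exposures. The Aim 2 analysis section says PHS child weight is used because matching adult data are available for calculating the systems-level exposures. The sampling section says that some adult-only measures will serve as LGA systems indicators. It is also a condensed article, and the respondent behind each factor score is the sort of detail a fuller plan may settle. For the sedentary, fruit and vegetable rows this objection stands: adult answers are a natural reading, and overlap there is only possible.

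It does not cure the two individual physical activity rows. Innate activity in childhood and the child item of parental modelling are child data by definition, the adult-data sentence is permissive, and the article itself fixes both the item list and the outcome.

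The objection to size also has force. The outcome is a set of guideline proportions, whereas the item is a level of activity. Parental modelling might enter as parent–child concordance rather than as raw child activity. Factor analysis presupposes correlated items. Domains are to be judged by AIC and BIC in a multilevel model, not by a 5% test of one correlation. The simulated rates therefore show direction and range and do not predict this model's error rate.

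A reader might infer that four of the five domains are contaminated and will be ranked above the physical activity environment. The documents show overlap in one domain, and no ranking has been demonstrated. A reader might also calculate 1/√8 = 0.35 and 2/√10 = 0.63, with rejection rates of about 44% and 95% at 26 LGAs. Those figures require mutually independent items and exact copies of the outcome, which the plan does not support.

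**Conclusion.** The point holds for the individual physical activity domain. As written, the third Aim 2 model has child physical activity on both sides, so that domain's contribution is biased towards a finding even if systems have no effect on child behaviour.

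The size cannot be fixed from the article. On the stated assumptions, false-positive rates run from about 6% to 49% with one overlapping item of eight and from about 10% to 99% with two, against a nominal 5%. They return to about 4% to 6% when the overlap is removed. For social psychology, individual psychology and food consumption the problem is conditional on child PHS responses being used.

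The reach is limited. One of the four hypothesis 2 models is affected. The randomised comparison of BMI z-score, hypothesis 1 and the outcomes of the other three models are not touched by this point.

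**What to change.** For the third model, compute the domain scores without any child-reported physical activity, sedentary, fruit or vegetable item. In practice:

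- drop *Degree of innate activity in childhood* and the child item of *Parental modelling of activity*;
- use adult responses for the PHS behaviour items in all domains, and state the respondent for each Table 3 item;
- add a general rule that no item may enter both a predictor domain and the dependent variable of the same model.

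This needs analysis wording and one alternative set of scores, and no new data. The cost is the loss of a few variables, and a domain definition in the third model that differs slightly from the other three. Refitting those three with the reduced scores as a sensitivity analysis would restore comparability across the series.
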